## LIST OF ABBREVIATIONS AND RELEVANT DEFINITIONS

|                |                                                                                                                                                                                                                                                                                                              |
|----------------|--------------------------------------------------------------------------------------------------------------------------------------------------------------------------------------------------------------------------------------------------------------------------------------------------------------|
| ABR     | ABR form, General Assessment and Registration form, is the application form that is required for submission to the accredited Ethics Committee (In Dutch, ABR = Algemene Beoordeling en Registratie)                                                                                                  |
| AE      | Adverse Event                                                                                                                                                                                                                                                                                         |
| AR      | Adverse Reaction                                                                                                                                                                                                                                                                                      |
| CA      | Competent Authority                                                                                                                                                                                                                                                                                   |
| CCMO    | Central Committee on Research Involving Human Subjects; in Dutch: Centrale Commissie Mensgebonden Onderzoek                                                                                                                                                                                           |
| CV      | Curriculum Vitae                                                                                                                                                                                                                                                                                      |
| DSMB    | Data Safety Monitoring Board                                                                                                                                                                                                                                                                          |
| EU      | European Union                                                                                                                                                                                                                                                                                        |
| EudraCT | European drug regulatory affairs Clinical Trials                                                                                                                                                                                                                                                      |
| GCP     | Good Clinical Practice                                                                                                                                                                                                                                                                                |
| HC      | Health Council                                                                                                                                                                                                                                                                                        |
| IB      | Investigator's Brochure                                                                                                                                                                                                                                                                               |
| IC      | Informed Consent                                                                                                                                                                                                                                                                                      |
| IMP     | Investigational Medicinal Product                                                                                                                                                                                                                                                                     |
| IMPD    | Investigational Medicinal Product Dossier                                                                                                                                                                                                                                                             |
| IPD     | Invasive Pneumococcal Disease                                                                                                                                                                                                                                                                         |
| METC    | Medical research ethics committee (MREC); in Dutch: medisch ethische toetsing commissie (METC)                                                                                                                                                                                                        |
| NIP     | Netherlands Immunization Program                                                                                                                                                                                                                                                                      |
| NP      | Nasopharyngeal                                                                                                                                                                                                                                                                                        |
| PCV     | Pneumococcal Conjugate Vaccine                                                                                                                                                                                                                                                                        |
| PCV7    | Prevenar®, 7-valent pneumococcal conjugate vaccine (Phizer/Wyeth)                                                                                                                                                                                                                                     |
| PCV10   | Synflorix®, 10-valent pneumococcal conjugate vaccine (GSK)                                                                                                                                                                                                                                            |
| PCV13   | Prevenar-13®, 13-valent pneumococcal conjugate vaccine (Phizer/Wyeth)                                                                                                                                                                                                                                 |
| (S)AE   | (Serious) Adverse Event                                                                                                                                                                                                                                                                               |
| SP      | Streptococcus pneumonia                                                                                                                                                                                                                                                                        |
| SPC     | Summary of Product Characteristics (in Dutch: officiële productinformatie IB1-tekst)                                                                                                                                                                                                                  |
| Sponsor | The sponsor is the party that commissions the organisation or performance of the research, for example a pharmaceutical company, academic hospital, scientific organisation or investigator. A party that provides funding for a study but does not commission it is not regarded as the sponsor, but |

referred to as a subsidising party.

**SUSAR** Suspected Unexpected Serious Adverse Reaction

**Wbp** Personal Data Protection Act (in Dutch: Wet Bescherming Persoonsgegevens)

**WMO** Medical Research Involving Human Subjects Act (in Dutch: Wet Medisch-wetenschappelijk Onderzoek met Mensen)

## SUMMARY

### Rationale:

*Streptococcus pneumonia* (SP) is an important cause of morbidity and mortality worldwide, with the highest incidence of disease among children < 2 years of age. *Streptococcus pneumonia* consisting of > 90 known different serotypes, of which a limited number of about 20 serotypes are known to cause invasive pneumococcal disease (IPD).

Prevenar®, a seven-valent pneumococcal conjugate vaccine (PCV7) was first introduced in the Netherlands immunization program (NIP) for children born after April 2006. It confers protection against serotypes 4, 6B, 9V, 14, 18C, 19F and 23F (see figure 1). It has been introduced in the NIP for vaccination at 2, 3, 4 and 11 months of age. Recently in 2009, two new vaccines were registered, which can in due time replace PCV7 in the NIP. All children born after March 2011 will receive Synflorix®, a ten-valent pneumococcal conjugate vaccine (PCV10) which confers protection against three additional serotypes. Prevenar-13®, a thirteen-valent pneumococcal conjugate vaccine (PCV13) confers protection against another three extra serotypes, but is not implemented in the NIP.

The current study in combination with our previous KOKKI (cellular immunogenicity after PCV7 vaccination) and PIM (comparison of 4 different PCV13 vaccination schedules based on humoral immunogenicity) study can give input to the Health Council (HC) on the best vaccination strategy for pneumococcal vaccination. The outcomes of this trial will provide data on the humoral and cellular immune response of PCV10 and PCV13.

### Objective:

Primary: To compare immunogenicity (humoral and cellular) induced by PCV10 and PCV13 after the booster dose of a complete vaccination series (3+1, the current NIP schedule)

### Secondary:

To compare immunogenicity (humoral) induced by PCV10 and PCV13 at 5, 8, 11 and 12 months of a complete vaccination series (3+1, the current NIP schedule)

To investigate the possible influence of the pneumococcal vaccination on the serological responses of other vaccine components of the NIP which are administered simultaneously in the other limb (DTaP-Hib)

**Study design:**

A controlled randomized intervention trial with 2 groups (see figure 2 and table 1).

- Group 1 PCV13
  - Divided in group 1a and 1b; 33 infants per group
- Group 2 PCV10
  - Divided in group 2a and 2b; 33 infants per group

Group 1 and 2 are split in sub groups in order to reduce the burden of the 8 ml blood samples. Randomization will be done within group 1 and within group 2.

**Study population:**

Children eligible to receiving the regular vaccinations of the NIP, born after August 2011 (assuring that all children are eligible for and will receive Hepatitis B vaccination)

**Intervention:**

Children of group 1 will receive the DTaP-IPV-Hib-HepB vaccination according to the NIP; they will receive PCV13 instead of PCV10. All vaccinations will be given by the study team during home visits.

Children of group 2 will receive all vaccinations (DTaP-IPV-Hib-HepB and PCV10) as part of the NIP by a well-baby clinic nurse; this is not part of the trial.

**Main study parameters/endpoints:**

Primary

***Pneumococcal serotypes***

- Cellular immune response (Plasma B cells and memory B cells) immediately before and 7-9 days after the booster at 11-months of age
- Humoral immune response (antibody concentrations and geometric mean concentrations (GMT)) at 12 months of age

Secondary

***Pneumococcal serotypes***

- Opsonophagocytoses immediately before and 7-9 days after the booster at 11-months of age
- Avidity at 5, 8, immediately before and 7-9 days after the booster at 11-months and at 12 months of age

- Antibody concentrations and geometric mean concentrations (GMT) at 5, 8, immediately before and 7-9 days after the booster at 11-months and at 12 months of age
- Kinetics of antibody concentrations and geometric mean concentrations (GMT) over time (at 5, 8, 11 and 12 months of age)

***DTaP-Hib***

- Antibody concentrations and geometric mean concentrations (GMT) at 5, 8, 11 and 12 months of age

**Nature and extent of the burden and risks associated with participation, benefit and group relatedness:**

One blood collection of 8 ml (2x 4 ml tubes). The burden and risk is considered low.

The children might find the needle scary and it might be painful but only for a few seconds. A local anaesthetic (Emla® crème, Astra Zeneca) may be used to minimize pain. Blood collection could result in a small bruise at the location of injection, which will disappear within a few days.

Group 1; one heel/finger stick sampling, group 2: 3-4 heel/finger sticks sampling. The burden and risk is considered low.

For group 2 (PCV10 group), the children themselves have no direct benefit in participating in this trial. The trial is aimed to study the immune response after 3+1 PCV10 or PCV13 vaccinations. These children, who have followed the Dutch NIP, are the only possible children that can participate in the trial. Visits will take 10-30 minutes each (depending on the type of blood collection and whether a questionnaire is taken).

Children in group 1 will receive PCV13 vaccinations. The side effects of these vaccinations are expected to be equal to the side effects of PCV10 (which the children would have received as part of the NIP). They will however receive these vaccinations at home to reduce the burden. These children will benefit from the added protection of the three extra serotypes which are not present in the PCV10 vaccination. These children are the only possible study group, since they are eligible for the Dutch NIP. Visits will take maximum 30 minutes each.

## 1. INTRODUCTION AND RATIONALE

*Streptococcus pneumoniae* (SP) is an important cause of morbidity and mortality worldwide, with the highest incidence of disease among children < 2 years of age. *Streptococcus pneumoniae* consisting of > 90 known different serotypes, of which a limited number of about 20 serotypes are known to cause invasive pneumococcal disease (IPD) such as bacteraemia, sepsis and meningitis, bone and joint infections or respiratory infections like pneumonia and otitis media (1). IPD is always preceded by nasopharyngeal (NP) pneumococcal colonization. In industrialised countries like the Netherlands, NP pneumococcal colonisation increases to 50% or more during the first year of life and remains high until the age of 3 years after which it decreases to a stable colonisation of 10-20% after 10 years of age (2, 3). NP carriage of infants and young children is an important source of organism transmission. In most cases pneumococcal carriers remain asymptomatic but they can develop severe airway infections or invasive disease.

As of June 2006 Pneumococcal Conjugate Vaccination (PCV) has been added to the Netherlands Immunization Program (NIP) for children born after April 2006. Prevenar®, a seven-valent pneumococcal conjugate vaccine (PCV7), was the first registered vaccine. It confers protection against serotypes 4, 6B, 9V, 14, 18C, 19F and 23F (see figure 1). It has been introduced in the NIP for vaccination at 2, 3, 4 and 11 months of age. Around 50% of European countries who use a PCV vaccine have introduced the vaccine in a 2+1 vaccination schedule (e.g. 2, 4 and 11 months of age or 3, 5 and 12 months of age). Recently in 2009, two new vaccines were registered, which can in due time replace PCV7 in the NIP. Synflorix®, a ten-valent pneumococcal conjugate vaccine (PCV10) confers protection against three additional serotypes (see figure 1). Prevenar-13®, a thirteen-valent pneumococcal conjugate vaccine (PCV13) confers protection against another three additional serotypes (see figure 1). Besides increasing serotype coverage of the three PCV vaccines, also the conjugate is different. Most\* serotypes of PCV10 are conjugated to protein D of non-typeable *Haemophilus influenzae*, instead of CRM197 carrier protein (conjugate for PCV7 and PCV13), which might influence the induction of memory. (\*except for type 18C who is conjugated to tetanus toxoid carrier protein and type 19F to diphtheria toxoid carrier protein)

As of March 2011 all newborns will receive PCV10 vaccinations instead of PCV7.

[figure not shown]

Figure 1 Serotypes present in the three pneumococcal conjugate vaccines

When comparing pneumococcal vaccines an IgG antibody concentration of  $\geq 0.35$  ug/ml is used according to the recommendations of the WHO expert committee on biological standardization (4). The antibody concentrations are generally measured at one month after the complete series.

PCV13 showed to be non-inferior to PCV7 for 6 out of 7 serotypes present in PCV7 (except for 6B), when comparing proportions of responders ( $\geq 0.35$  ug/ml) and geometric mean concentrations (see SPC of PCV13 and (5)). In addition it was shown that PCV13 elicits OPA responses comparable to those elicited by PCV7.

PCV10 induces slightly lower antibody concentrations than PCV7 but are similar in terms of % responders (see SPC of PCV10 and (6)).

PCVs are thought to induce immediate protection through stimulation of antibody production by polysaccharide specific plasma B cells, sustained protection is conferred by a memory B cell pool which induces an accelerated increase in antibody concentrations during secondary immune responses seen after re-infection or boosting. Both the induction and maintenance of functional serum antibody concentrations have a cellular basis which is still poorly understood.

In general, antigens trigger naïve B-cells to expand and differentiate into two types of affinity matured B-cells: antibody secreting plasma B cells and memory B-cells. This immunological B cell priming occurs in highly organized structures of lymphoid tissues, under the influence of cognate CD4+ T cell help. Since plasma cells are unlikely to persist for more than 6-8 weeks (7) maintenance of steady state antibody levels over periods of years requires a continuous low level of differentiation of memory B cells into plasma cells. Factors such as recurrent antigen exposure for example through carriage might be involved in this process.

Carriage of the 7 serotypes present in PCV7 has decreased since the introduction of PCV in the NIP. This can influence the induction of memory and plasma B-cells, since there is hardly any natural boosting. Some of the extra serotypes present in PCV10 and PCV13 are still influenced by the natural boosters.

**General aim of our pneumococcal projects is to determine the most optimal pneumococcal vaccination program for the NIP**

The number of vaccinations (2+1 versus 3+1), timing of vaccinations and the product choice depend on several factors such as;

- Humoral immunity, which is determined by the measurement of antibody response
  - Protection in the period of peak incidence of IPD (~8 months of age)
  - Protection after the booster
  - Kinetics of antibody concentrations over time
  - Percentage of antibody concentrations above the correlate of protection threshold
- Cellular immunity, which is determined by the measurement of plasma and memory B-cells, opsonophagocytoses and avidity
  - The vaccination schedule should lead to a sustained protection
  - Decrease in carriage (natural boosting) might lead to lower memory responses
  - Different conjugates can lead to differences in memory responses
    - PCV13 is an extended version of the PCV7 vaccine, 6 serotypes are added and both vaccines are conjugated to CRM197 carrier protein
    - PCV10 has a different conjugate, protein D of non-typeable *Haemophilus influenzae*
- Vaccine composition
  - Coverage of the products, especially in the Dutch population; PCV13 confers protection to more serotypes than PCV10

### **KOKKI, PIM and our current study**

An improved understanding of the immune biology of the conjugate vaccines, such as PCV10 and PCV13, is essential to develop the best immunization strategies that provide sustained protection. The results from the cellular immunity and the antibody concentrations will help to decide on the best vaccination strategy for pneumococcal vaccination in the NIP. The current study in combination with our previous KOKKI and PIM studies will provide more information for the optimization of the pneumococcal immunization program.

### **Cellular immunity**

The aim of **our previous study** (KOKKI, cellular immunogenicity after PCV7 vaccination (NL24329.000.08), 2009) was to determine the development of the cellular immune response (plasma B cells and memory B-cells) for the 3+1 vaccination schedule of PCV7. Since 2009 several factors have changed:

- PCV10 has been introduced in the NIP (instead of PCV7)
- PCV13 was registered and might become part of the NIP in the future

- Carriage of the serotypes present in PCV7 have decreased in the five years following introduction of PCV7 in the NIP (2006), leading to loss of natural booster, and possibly lower memory responses

We lack information on the memory response to PCV10 and PCV13, therefore **our current study** aims to determine the development of the cellular immune response (plasma B cells and memory B-cells) for the 3+1 vaccination schedule of PCV10 and PCV13 immediately before and 7-9 days after the booster at 11-months of age. Time points of blood collection are similar to those in the previous KOKKI study. Also the antibody concentrations, avidity and opsonophagocytoses will be determined at these time points. These vaccines differ in number of serotypes and type of conjugate and could therefore differ in their cellular immunity.

A selection of 5-6 serotypes will be made; two of the four serotypes tested in the KOKKI study and three to four serotypes added by PCV10 and PCV13 for the current study. Selection will depend on serotype circulation just before analyses.

### **Humoral immunity**

The aim of **our previous study** (PIM, (NL28918.000.09), 2010-2012), was to assess the optimal PCV vaccination schedule for PCV13, based on humoral immunogenicity after four different vaccination schedules.

An alternative timing and reduction of the number of vaccination doses on the serological response directed against the different serotypes of pneumococci was compared to the currently used\* 3+1 vaccination schedule. The schedules were two 2+1 vaccination schedule (2, 4 and 11 months of age; 3, 5 and 11 months of age) and two 3+1 vaccination schedules (\*2, 3, 4 and 11 months of age; 2, 4, 6 and 11 months of age).

After the start of the study PCV10 was introduced in the NIP and not PCV13. It is therefore important to compare the vaccines for the currently used 3+1 vaccination schedule. Also universal vaccination against Hepatitis B will be introduced for children born after August 2011, and therefore the DTaP-IPV-Hib vaccine will be replaced by DTaP-IPV-Hib-HepB, which could influence the response to PCV13.

**The current study** will investigate the humoral immunogenicity of PCV10 after the currently used 3+1 vaccination schedule (vaccination at 2, 3, 4 and 11 months of age). The data will be compared to the 3+1 vaccination schedule of PCV13 (PIM study). To rule out the influence of the shift from DTaP-IPV-Hib to DTaP-IPV-Hib-HepB vaccine we will use data from group 1 (PCV13) of the current study, to bridge both studies.

As in the PIM study blood samples are collected at one month after the primary series (5 months), at 8, 11 and 12 months of age. The 12 months sample is used to compare the schedules (primary endpoint). The 8 month sample is chosen, since the peak incidence of

IPD is around 8 months. The 5, 8, 11 and 12 month time points are used to assess the kinetics of antibody concentrations in time. To look for interference of concurrent vaccinations DTaP-Hib will be tested.

Hypothesis used for this study:

PCV10 and PCV13 are comparable in inducing cellular and humoral immune responses in Dutch infants. Differences are expected between serotypes; the 7 serotypes of PCV7 are not under influence of natural boosting; the new serotypes present in the vaccines are still under influence of natural boosting.

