## 2. OBJECTIVES

Primary: To compare immunogenicity (humoral and cellular) induced by PCV10 and PCV13 after the booster dose of a complete vaccination series (3+1, the current NIP schedule)

Secondary:

To compare immunogenicity (humoral) induced by PCV10 and PCV13 at 5, 8, 11 and 12 months of a complete vaccination series (3+1, the current NIP schedule)

To investigate the possible influence of the pneumococcal vaccination on the serological responses of other vaccine components of the NIP which are administered simultaneously in the other limb (DTaP-Hib)

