#### 4.4 Sample size calculation

For **cellular immunity**: each group will contain 25 evaluable children (based on previous experience we expect to include at least 30 children in order to reach 25 evaluable children). The group size is based on the previous KOKKI study (NL24329.000.08).

*'The clinical meaning of differences between the numbers of memory B-cells is still unknown. Therefore power calculations are at the moment not possible. Previous research has shown that the number of memory-B cells circulating in blood is very low before a booster vaccination and in order to observe a trend after revaccination a group of 22 children is needed (including a possible 10% loss of subjects' leads to 25 children for each group).'*

In the KOKKI study, for each child blood was collected at one time point only, being either pre- or 7-9 days post-booster. Inclusion and blood collection was during the same visit. Inclusion in the current study however starts at first vaccination, respectively 9 (group 1) and 6 (group 2) months prior to blood collection for cellular immunity, which can lead to a higher amount of dropout. Taking into account a 10% dropout up to 11 months, we included 33 children in each group. A subsequent estimated failure rate to collect sufficient blood cells of 15% will generate 25 evaluable children.

**Antibody concentrations** will be compared between the PCV10 group of the current study and the PCV13 group of the PIM study (vaccination schedule 2, 3, 4 and 11 months) at 12 months after vaccination. As significance level we take 0.05 two-sided and as power 80%. The expected variance of log(GMC) is 0.27 (this is for serotype 6B, the serotype with the highest variance). Using the following formula  $n = 2k^2\sigma^2 / \delta^2$ , we need 47 children per group to detect a 2-fold difference in GMC (=0.30 difference in log(GMC)) between the two groups. A 2- to 2.5-fold difference is considered to represent a true difference in immunogenicity in this type of study (8,9). To account for 20% dropout, 59

children need to be included per group. As we already include  $2 \times 33 = 66$  children in the cellular immunity part of the study, this group is also large enough to assess antibody concentrations.

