## 9. STATISTICAL ANALYSIS

### 9.1 Descriptive statistics

Baseline comparability of the groups will be shown by descriptive statistics and frequency tables (e.g. with information as gender, age, day care attendance etc).

Little is known about cellular immune responses against *Streptococcus pneumonia* quantitative endpoints of this study.

Frequencies of pneumococcal specific B cell populations (number of cells per  $10^6$  PBMC) and antibody concentrations (U/ml) will be calculated per patient.

B cell frequencies will be shown in medians and will be compared using non-parametric Mann-Whitney test. Results of antibody levels are expressed in geometric mean concentration (GMC) with 95% confidence interval (95% CI). Statistical differences in IgG GMC values will be assessed by log transformed unpaired t test. Correlations between IgG levels and circulating B cells will be assessed by Spearman correlation. All reported p-values are 2-sided, p-values smaller than 0.05 are considered significant. Analyses will be performed with SPSS 15.0 and PRISM4.

Other more qualitative endpoints, such as avidity and opsonophagocytoses, will be described as such.

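### The stated hypothesis is that PCV10 and PCV13 are comparable, but the study is sized and analysed only to detect a difference, so a non-significant result cannot support it

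*Protocol*

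**What the plan says.** Section 1 (Humoral immunity) gives the study hypothesis as "PCV10 and PCV13 are comparable in inducing cellular and humoral immune responses in Dutch infants", and adds that differences between serotypes are expected. Section 2 is neutral: "Primary: To compare immunogenicity (humoral and cellular) induced by PCV10 and PCV13 after the booster dose of a complete vaccination series".

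Section 4.4 sizes the humoral comparison as a difference test: two-sided 0.05, 80% power, 47 evaluable children per group for a 2-fold difference in GMC. On variability it says "The expected variance of log(GMC) is 0.27", the value for serotype 6B, the most variable. On relevance it says "A 2- to 2.5-fold difference is considered to represent a true difference in immunogenicity in this type of study". The comparison is between the PCV10 group of this study and the PCV13 group of the PIM study on the same schedule. The same calculation is reused for the bridging comparison of this study's PCV13 group with PIM.

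For cellular immunity, section 4.4 says the clinical meaning of a difference in memory B cells is unknown and a power calculation is not possible. The group size comes from the KOKKI study: "in order to observe a trend after revaccination a group of 22 children is needed".

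Section 9.1 fixes an unpaired t-test on log IgG and a Mann-Whitney test for B cells. The 95% CI it mentions belongs to the GMC. Its only decision rule is "All reported p-values are 2-sided, p-values smaller than 0.05 are considered significant". Section 9.2 adds chi-square tests and t or distribution-free tests, all for differences.

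**The concern.** A difference test that fails to reach 0.05 shows only that the data did not exclude a ratio of 1. It does not show that the ratio is close to 1. To support comparability, the interval for the PCV10/PCV13 ratio has to exclude differences that matter, and the protocol neither plans that interval nor names a bound. The 2-fold figure sets the sample size and then plays no part in the analysis.

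Two readings of the results are left unguarded. A non-significant serotype may be taken as confirming the hypothesis when the data still allow a 2-fold gap. A significant serotype may have an observed ratio well below what section 4.4 treats as a true difference. The bridging comparison has the first problem too: section 1 uses it to exclude an effect of the switch to the HepB-containing vaccine, which is a claim of no difference.

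**Working it through.** **Inputs.** From section 4.4: variance of log10 concentration 0.27, difference 0.30 (log10 of 2 = 0.301), two-sided 0.05, 80% power, 20% dropout, 66 children enrolled per vaccine. The size of the PIM group is not stated and is assumed equal. Normal quantiles are used.

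**1. The plan's own figure.** n = 2k²σ²/δ² with k = 1.96 + 0.84:
- δ = 0.30 gives 47.09, and δ = 0.301 gives 46.8, so 47.
- Dropout: 47/0.80 = 58.75, so 59.

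Both reproduce, as a two-sided difference calculation. With 66 enrolled, 66 × 0.80 is about 53 evaluable.

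**2. Standard error of the log10 ratio.** SE = √(2 × 0.27/n):
- n = 47: 0.107
- n = 53: 0.101

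**3. Smallest significant observed ratio.** 10^(1.96 × SE):
- n = 47: 1.62
- n = 53: 1.58 (1.59 with the t quantile)

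**4. Largest observed ratio whose 95% CI excludes 2-fold.** 10^(0.301 − 1.96 × SE):
- n = 47: 1.23
- n = 53: 1.27

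At 53 per group, observed ratios from 1.27 to 1.58 are therefore non-significant while the CI includes 2. For example, an observed ratio of 1.40 (log10 0.146) has limits 0.146 ± 0.198, which is 0.89 to 2.21.

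**5. Chance of p ≥ 0.05 when a difference exists.**

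| True ratio | 47/group | 53/group |
|---|---|---|
| 2.0 | 20% | 15% |
| 1.5 | 62% | 59% |

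**6. Chance of showing comparability within 2-fold if the true ratio is 1.** 2Φ(0.301/SE − z) − 1, with z = 1.96 for a 95% CI and 1.645 for a 90% CI:

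| Evaluable per group | 95% CI | 90% CI |
|---|---|---|
| 47 | 60% | 76% |
| 53 | 69% | 82% |

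These are per serotype at the highest variance, so less variable serotypes do better. The bound matters: 80% probability needs 63 (95% CI) or 52 (90% CI) evaluable per group at 2-fold, but only 36 or 30 at 2.5-fold.

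**7. Cellular endpoint.** No bound can be derived from the protocol. With 25 against 25 evaluable children, Noether's formula gives (p − 0.5)² = 7.85/(3 × 50) = 0.052. The Mann-Whitney test therefore reaches 80% power only when P(X>Y) is about 0.73. A null result there says little about similarity.

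**The case against.** The strongest reply is that the mismatch lies in one introductory sentence. The objective is to compare, the sample size is for detecting a difference, and the tests are for differences, so the operational design is coherent. The hypothesis may be meant as a null hypothesis, and the protocol nowhere promises to treat p ≥ 0.05 as proof. This has force. It is why rewording the hypothesis is an acceptable repair. But the sentence is labelled as the study hypothesis, and as written the plan cannot support it.

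It can also be said that a ratio with its CI follows from the planned t-test and could be left to a statistical analysis plan. That is fair for the reporting format. It does not cover the decision rule, which the protocol itself fixes at p < 0.05.

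Several stronger readings are tempting but not supported:
- A reader might take 2-fold as the protocol's own equivalence margin. Section 4.4 gives a 2- to 2.5-fold range to justify the effect to detect. No margin is stated.
- A reader might infer that a verdict of comparable or not goes straight to the Health Council. The Summary says only that this study, together with KOKKI and PIM, can inform the best strategy, and section 1 lists other factors.
- A reader might think the three PCV13-only serotypes distort the result. Section 4.4 analyses each serotype on its own and disclaims interest in an overall null, so there is no pooled verdict to distort.
- A reader might assume that null cellular results will be reported as equal memory. The protocol does not say so, and it discloses that the meaning of a difference is unknown.

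**Conclusion.** The point holds in this limited form: the hypothesis is comparability, the design and analysis are for a difference, and a non-significant result cannot support the hypothesis. At variance 0.27 and 53 per group, the gap covers observed ratios of about 1.27 to 1.58. The rule can also call an observed ratio of about 1.6 significant, below the range that section 4.4 treats as a true difference.

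The stated 80% power is correct for detecting 2-fold, but it is not the probability of showing comparability. That probability is about 60% to 69% with a 95% CI, or 76% to 82% with a 90% CI. These figures rest on a 2-fold bound, a true ratio of 1, a PIM group of equal size and the highest variance. A 2.5-fold bound would give higher values.

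The difference test itself is not wrong and should stay. A reader might go on to propose declaring a difference only when the whole CI lies outside 0.5 to 2.0. That would flag a true 2-fold difference only about 2.5% of the time, against the planned 80%, and would undo the design.

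**What to change.** - **Sections 9.1 and 9.2:** keep the planned tests and add the PCV10/PCV13 GMC ratio with its CI for each of the ten shared serotypes. State that p ≥ 0.05 will not be read as comparability. Use the word comparable only if the CI lies within one prespecified bound chosen from the 2- to 2.5-fold range, and state the confidence level.
- **Or section 1:** reword the hypothesis as estimation of differences between the vaccines, with no claim of comparability.
- **Section 4.4:** say that the 80% power is for detecting a 2-fold difference. If comparability is kept, give the probability of showing it, with the actual PIM group size.
- **Bridging comparison:** read it in the same way, from the ratio and its CI.
- **B cells:** report the between-vaccine difference with a CI and make no claim of comparability.

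The cost is a change of wording, a little more analysis and a less favourable stated power for comparability. No extra children are needed.
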